### Project phases

This is the second phase of a recently completed project (phase 1; figure 1), developed in line with the Medical Research Council framework for developing and evaluating complex interventions.^46^ Phase 1 of Co-STARS involved the co-production of the training package with young people from Black African and Black Caribbean backgrounds with lived experience of mental ill health. Interviews and focus groups with mental health professionals were also conducted to assess existing knowledge and identify areas where training interventions were necessary. Phase 1 of the Co-STARS programme (2023–2024) focused on the co-production of the training content and format through workshops and focus groups with Black young people, mental health professionals and community leaders. This formative phase identified key barriers to equitable care and generated the two training components evaluated in the current Phase 2 feasibility study (WP1 and WP2).

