## Methods and analysis

Trial status: Phase 2 trial recruitment started in March 2025 and is due to conclude in January 2026.

Phase 2 aims: We aim to undertake a pilot evaluation assessing the feasibility, acceptability and cost-effectiveness of a MHL package designed to promote equitable mental healthcare access and improve outcomes for underserved groups. We co-designed and co-developed the following work packages (WP; figure 2) based on close engagement with stakeholders and patient and public involvement and engagement (PPIE) :

WP1: Pilot CRT of lived experience-led MHL training in community settings.WP2: Pilot Stepped Wedge Cluster Randomised Trial (SWCRT) of e-learning for mental health professionals.WP3: Mixed-methods study: Systems mapping and systems change evaluation.WP4: Economic evaluation of WP1-3 to develop a framework to examine cost-effectiveness and social return on investment (SROI).

In addition to assessing impact, we will embed a mixed-methods realist-informed process evaluation to explore the mechanisms of change and resources required to support intervention reach and impact in the continued rollout. We will develop theories that explain how outcomes targeted by Co-STARS are achieved, for whom, why and under what circumstances (contexts). The process evaluation will comprise targeted searches for literature, using the principles of a realist synthesis, interviews with various groups of stakeholders and a document review. The process evaluation will be critical to understand how the implementation is achieved, how each of the interventions produces change and how context might affect implementation and outcomes, including impact on mental health inequalities. Although effectiveness will not be tested at this stage, a pilot randomised design is essential to evaluate feasibility of recruitment, randomisation, data collection and implementation procedures of this intervention. These feasibility outcomes will determine whether progression to a definitive multi-site effectiveness trial is justified and inform its design.

A completed SPIRIT 2025 checklist is provided as online supplemental material 1, detailing the corresponding page and line references within this protocol.

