#### WP1: pilot CRT of lived experience-led MHL training in community settings

Research question: Can a lived experience-led, community-delivered MHL training package be feasibly implemented and accepted within underserved Black communities?

Design: Pilot CRT assessing feasibility, acceptability and preliminary change in mental health knowledge, attitudes and help-seeking.

Objective: To assess the feasibility and acceptability of the MHL intervention delivered to underserved communities and assess the barriers and enablers to support the future implementation strategy/trial.

Design: An unblinded, pragmatic, feasibility CRT implemented within a specific underserved community in Birmingham. We will adhere to the CRT consort extension^47^ to ensure transparency and quality of reporting. A mixed methods realist approach will be adopted for the process evaluation.

Method: Recruitment of clusters and implementation of the intervention will occur over a 6-month time frame (months 4–9). Participants within the cluster will be consented and asked to complete pre-outcome/post-outcome measures. We will also conduct structured observations assessing the fidelity of intervention delivery, as well as two focus groups and semi-structured interviews with participants within the control and intervention arms, as well as young people delivering the training.

Data collection schedule: Baseline data will be collected immediately prior to training (T0), and follow-up data 3 weeks post-intervention (T1). Research assistants trained in Good Clinical Practice will oversee all data collection, supervised by the principal investigator.

Setting: We will target two constituencies in the West region of Birmingham and Black Country region. The West of Birmingham is a region with the highest proportion of Black African and Black Caribbean individuals in Birmingham (19% compared with 9% and 3.5% in Birmingham and UK, respectively), with over half of the population living in the top 10% decile for deprivation, meaning that these communities are likely exposed to a multitude of social risk factors for development of severe mental illness.^42^

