#### WP2: a pilot SWCRT of e-learning for mental health professionals

Research question: Is an e-learning module on culturally responsive care feasible and acceptable for delivery to NHS mental health professionals?

Design: Pilot stepped-wedge cluster randomised trial assessing feasibility, uptake and change in multicultural competence scores.

Aims and objectives: To evaluate the feasibility and acceptability of the e-learning to inform our implementation evaluation in a future trial (phase 3).

Design: We will adopt a pragmatic SWCRT^60^ design with random and sequential crossover of clusters (youth mental health teams) from control to intervention (our e-learning module) until all clusters are exposed. Because training is delivered openly within existing clinical teams, outcome assessment cannot be blinded; feasibility endpoints are objective and carry minimal risk of bias.

Methods: There will be a phased and sequential implementation of the e-learning at regular intervals across teams and trusts over a 6-month period (months 4–9; figure 3). Staff will complete the training outcome measure before and after the e-learning.

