This pilot evaluation will be undertaken in three phases: (1) Identification of suitable data sources: Guided by health data science expertise in the research team, expert opinion from the systems mapping process and through open source searching, we aim to compile a directory of suitable datasets and outcomes which could inform the systems wide impact of the intervention. For example, West Midlands Police Data will be used to examine the rate of detentions under Section 136 of the UK Mental Health Act among Black males. These detentions represent police-initiated transfers of individuals appearing mentally unwell from public settings to a place of safety for clinical assessment. Data sources will include open-access administrative datasets (eg, NHS Digital, West Midlands Police s136 statistics) and local health service indicators, each evaluated for completeness and temporal resolution before inclusion. (2) Trial of ITS model: Using available datasets (those open access or those already accessible by the research team), we will undertake a pilot ITS. The study period will be set between 2022 and 2024. Incidence rates (calculated by the number of new cases divided by the at-risk population) will be analysed on a monthly basis (weekly where possible) throughout the study period and these trends will be depicted graphically. The primary break point that will be examined is the introduction of the intervention; thus, monthly data 1 year prior and 1 year following this timepoint will be included. We will examine the sensitivity of the analysis around this break point. (3) Stakeholder engagement: We plan to undertake three focus groups (consisting of six to eight people) with key stakeholders (patients, providers and commissioners) to demonstrate our findings from the trial to unpick the possible mechanisms for these changes as a result of the impact of the intervention of the systems map. The secondary aim of these focus groups will be to optimise the strategy to undertake such systems change evaluation of a broader scale when the intervention is rolled out for a full trial.

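### The WP3 interrupted time series is dated 2022–2024, but the intervention it takes as its break point cannot have begun before March 2025, so the stated window holds no post-intervention month

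*Protocol article*

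**What the plan says.** The WP3 section (systems mapping and systems change) describes a pilot ITS on routine data, for example police detentions under Section 136. Its stated aim is to find out whether introducing Co-STARS changes the outcomes that the systems mapping identifies. The second stage, the trial of the ITS model, fixes three things:

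- the calendar period: "The study period will be set between 2022 and 2024";
- the break: "The primary break point that will be examined is the introduction of the intervention";
- the data around the break: "monthly data 1 year prior and 1 year following this timepoint will be included".

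The timing of the intervention is given elsewhere in the article:

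- Methods and analysis, Trial status: "Phase 2 trial recruitment started in March 2025 and is due to conclude in January 2026".
- WP1, data collection schedule: "Baseline data will be collected immediately prior to training (T0), and follow-up data 3 weeks post-intervention (T1").
- WP1, Method: "Recruitment of clusters and implementation of the intervention will occur over a 6-month time frame (months 4–9"). WP2 gives the same months for the staggered e-learning and has staff complete the outcome measure before and after it. The article gives no calendar date for month 1.
- Project phases: "Phase 1 of the Co-STARS programme (2023–2024) focused on the co-production of the training content and format".

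**The concern.** An ITS estimates an effect by comparing the series after a known date with the course projected from before it. It needs observations on both sides of that date. Here the calendar period appears to close before the date arrives.

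This would leave WP3's quantitative impact analysis impossible to carry out as described. Two rules in one paragraph give the analyst incompatible instructions, and the choice between them decides whether the analysis says anything about Co-STARS. In the third stage the findings go to focus groups of patients, providers and commissioners, who are asked to discuss mechanisms for changes attributed to the intervention. A series with no post-intervention data cannot support that discussion.

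**Working it through.** **Inputs.** Window: January 2022 to December 2024, the widest reading of the stated years (WP3). Required span: 12 months before and 12 months from the break (WP3). Earliest break: March 2025, because recruitment began then (Trial status) and baseline precedes training in WP1 and WP2. Only Phase 1 co-production is placed in 2023–2024, and no section describes earlier delivery of either training component.

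**Month index.** k = 12 × year + (month − 1).

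- January 2022: 12 × 2022 + 0 = 24264
- December 2024: 12 × 2024 + 11 = 24299
- Window length: 24299 − 24264 + 1 = 36 months
- March 2025: 12 × 2025 + 2 = 24302

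**Can the plan's own window be reproduced?** A break b with 12 + 12 months inside the window needs b − 12 ≥ 24264 and b + 11 ≤ 24299, so 24276 ≤ b ≤ 24288. That is January 2023 to January 2024. The latest such date is 24302 − 24288 = 14 months before recruitment started, so the stated window cannot be obtained from the stated break.

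**Overlap with the required months.** For a March 2025 break the pre-months are 24290 to 24301, of which 24290 to 24299 (10 months) lie in the window. The post-months are 24302 to 24313, of which none does. Because month 1 is undated, the count is repeated over a range of break dates. The June, August and November rows assume that month 1 is March 2025.

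| Break | Required 12 + 12 span | Pre-months in window | Post-months in window |
|---|---|---|---|
| March 2025 (earliest) | Mar 2024 – Feb 2026 | 10 of 12 | 0 of 12 |
| June 2025 (month 4) | Jun 2024 – May 2026 | 7 of 12 | 0 of 12 |
| August 2025 (month 6) | Aug 2024 – Jul 2026 | 5 of 12 | 0 of 12 |
| November 2025 (month 9) | Nov 2024 – Oct 2026 | 2 of 12 | 0 of 12 |
| January 2026 (end of recruitment) | Jan 2025 – Dec 2026 | 0 of 12 | 0 of 12 |

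**Estimability.** The article gives no regression form, so take the usual segmented model as an illustration: E(Y_t) = β0 + β1·t + β2·D_t + β3·D_t·(t − b), with D_t = 1 when t ≥ b and 0 otherwise. On January 2022 to December 2024, D_t = 0 in every month. The columns for β2 (level change) and β3 (slope change) are all zero, and the design has rank 2 of 4. On a 12 + 12 span around the break the rank is 4 of 4. Any other model with a step or slope term at the break fails in the same way on the stated window.

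**The case against.** The strongest defence concerns weight. WP3 calls the time-series work exploratory and a pilot. Methods and analysis says effectiveness is not tested at this stage and that feasibility outcomes decide progression, and no WP1 or WP2 feasibility outcome uses the ITS. This stands and lowers the severity. It does not remove the conflict, because the stated aim is still to detect a change after introduction, and a series without a post period cannot pilot a break-point model either.

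A second defence is that the 12 + 12 rule is tied to the intervention date. An analyst who followed it would have post-intervention data, and the years would simply be out of date. That is a plausible account of how the conflict arose. It is also why the supportable claim is that the two rules must be reconciled, and not that the analysis will necessarily be run without post data.

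The planned sensitivity analysis around the break does not help. To include even one month on or after the break, the break would have to move from March 2025 to December 2024, when nothing under evaluation was being delivered.

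A reader might infer three stronger points, and the document does not support them:

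- *That data from before the 12 pre-months are thrown away.* The article says a year on each side is included and that rates are analysed over the whole study period. It does not say other months are excluded.
- *That seasonality would defeat a 12 + 12 design.* No regression form or seasonal amplitude is given, and the handling of seasonality is commonly left to an analysis plan, which is not shown here.
- *That a spurious break will be reported as a Co-STARS effect.* On the stated window the terms at the intervention date are not estimable, so no effect at that date could be reported. A misreading would require a break to be sought at some other date.

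**Conclusion.** Wrong as written, of moderate severity. The year range contradicts the break-point rule in its own paragraph once the recruitment date is read alongside it. The result does not depend on the undated month 1: the post-intervention count is 0 of 12 for every break from March 2025 onward.

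The conclusion rests on one inference, that delivery cannot precede recruitment. The baseline-before-training sequence in WP1 and WP2 supports it, and nothing in the article contradicts it. The point does not touch the WP1 or WP2 feasibility outcomes or the progression decision. It limits what the ITS can conclude and what can properly be put to stakeholders.

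**What to change.** Replace the fixed years with a period defined by the actual date of first delivery. Suggested content:

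> The ITS will use monthly data from January 2022 to at least 12 months after the break point. The break point is [calendar date], defined as [the chosen event in the months 4–9 roll-out], and is no earlier than March 2025. All available months from January 2022 up to the break form the pre-period.

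For a March 2025 break the series runs to February 2026 or later; for a June 2025 break, to May 2026 or later. The event that defines the break must be named because WP1 and WP2 are both delivered over several months and the e-learning is staggered by team, so the date of introduction is not unique.

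If 12 post-introduction months cannot be obtained within the project, say so, and state that only the pre-intervention model is piloted and that no impact of Co-STARS will be inferred or presented to the stakeholder focus groups.

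The cost is a few sentences in the protocol and a later extract of the routine data. The downside is small: the ITS result, and the focus groups that use it, come later.

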#### WP4: economic evaluation to examine cost-effectiveness and SROI

Research question: What are the costs and potential cost-consequences of implementing the Co-STARS tiered training approach?

Design: Economic evaluation and SROI analysis based on feasibility trial data.

Our approach is likely to reduce direct health costs (admission and healthcare usage), but it could also have important cost implications for the healthcare sector, public sector and voluntary sectors. The primary outcome for the economic evaluation will be the incremental cost per unit improvement in MHL (community participants, WP1) and multicultural competence (NHS staff, WP2). Secondary outcomes will include changes in rate of mental health incident rates, quality of life, healthcare utilisation and social value generated, assessed using a SROI framework. The primary base case analysis will adopt a public sector perspective in line with NICE guidelines, with a wider societal perspective explored as a secondary analysis. Uncertainty in cost and outcome estimates will be addressed using deterministic and probabilistic sensitivity analyses, with results presented as 95% CIs and cost-effectiveness acceptability curves. This feasibility-stage economic evaluation will not test intervention effectiveness; rather, it will develop a cost-effectiveness framework and examine the practicality of collecting cost and outcome data within pilot conditions. Preliminary cost-consequence estimates using the data collected in line with the framework developed will be used to inform the design and analytic framework of the definitive Phase 3 trial.

Data collection: First, and most relevant to WP1 and WP2, resource use data will be used to estimate the costs associated with each of the intervention and control arms. This will include (i) intervention costs; (ii) healthcare resource use; (iii) wider public sector resource use; and (iv) private costs. Information on unit costs or prices will be sourced to attach to each resource use item, to enable an overall cost to be calculated (eg, Personal Social Services Research Unit (PSSRU) Unit Costs of Health and Social Care).

Cost-effectiveness: To compare intervention arms with the control, a within-study analysis and a model-based economic analysis will be undertaken. This will primarily use the data collected within the trial. Initially, the base case analysis will be framed in terms of a cost-consequences analysis, and data will be reported in a disaggregated manner on the incremental cost and important consequences assessed in WP1 and WP2. The main economic analysis will assess the feasibility of undertaking a cost-effectiveness analysis based on the costs and health outcomes collected in WP1 and WP2. The economic evaluation will be conducted and reported in accordance with relevant guidelines (eg, Consolidated Health Economic Evaluation Reporting Standards (CHEERS) checklist) and recommended methodologies.^67 68^ If this is found to be feasible, this will drive the cost-effectiveness analysis for a trial and future real-world settings if the intervention is widely adopted.

SROI: As not all costs are quantifiable, we will also explore an SROI.^69^ Our youth advisory group (and work undertaken during phase 1) will help us determine which items (including ones where costs are intangible) matter and discuss how they should be quantified. This is particularly relevant when considering the wider system impacts in response to the intervention (eg, the impacts of improved community connectedness).

### Patient and public involvement and engagement

This programme of work from conception through to delivery has been informed by PPIE, including young people with lived experience and our charitable partners who have provided advice on study management, training and support for PPIE, as well as inputting into the lay summary. This study represents phase 2 of a three-phase project, and engagement with young people with lived experience of mental health difficulties began during earlier consultation work and the QR-funded phase (phase 1). Young people from Black African and Black Caribbean diaspora communities contributed to shaping the research questions, intervention design and evaluation approach. Co-production workshops informed the selection of outcome measures, including acceptability of training, cultural responsiveness and community engagement outcomes. Public contributors also helped develop recruitment materials (eg, flyers and wording), training content and study procedures, and advised on the feasibility and participant burden of study procedures, including questionnaire length, training duration and follow-up interviews.

We have ensured good practice in line with UK Standards for Involvement.^61 70^ We have also appointed a diverse youth advisory group who will work closely with the research team to inform on project ethics, delivery and dissemination. The group consists of young people from Black African and Black Caribbean diaspora residing in Birmingham, and who have lived experience of mental ill health. We have also established a Research Advisory Committee comprising external researchers and relevant community stakeholders, including Community Network Support Officer, NHS Trust staff, faith leaders, representatives of Birmingham Voluntary Services Council and West Midlands Violence Reduction Partnership.

In phase 2, persons with lived experience will also contribute to the delivery of the MHL training alongside the research team. Persons with lived experience are included as co-authors and contributors to this protocol and will continue to contribute to interpretation and dissemination of findings through youth advisory meetings, community workshops and partner organisations, including voluntary sector and NHS networks. Youth contributors will be reimbursed for their involvement.

## Ethics and dissemination

This study is implemented as four work packages. The participants in all work packages will receive a participant information sheet and informed consent form prior to giving their informed written consent. The participants have the right to refuse to participate or to withdraw their consent at any time after giving their consent. The participant information sheet includes an introduction to this research, reason for the selection of participants, participants’ involvement in research, potential benefits and risks of taking part in this research, reimbursement of time and expenses, information on the organisers, insurers, funders, reviewers of this study, confidentiality, use of personal information and sources to get additional information. This also includes a detailed account on whom to report any problems. All quantitative data will be entered into secure University of Birmingham servers with restricted access. Identifiable information will be stored separately from research data, and qualitative recordings will be pseudonymised and transcribed using approved university services. Data monitoring and coding will follow the Data Protection Act 2018 and General Data Protection Regulation (GDPR) compliance.

